## Methods/Design

### Study design

The process of allocation to the two housing programs was determined by needs analyses conducted by the case workers who engaged with homeless individuals in the designated catchment area of inner Sydney. Given this process, a control group was not a feasible option and an ecological study was selected which utilised a longitudinal, mixed methods design. Housing and health outcomes were compared at baseline and 12 months follow-up of the scatter site (Platform 70) and congregated site (Common Ground) programs. The methodology, conduct and reporting of this study is in accordance with the Strengthening the Reporting of Observational Studies in Epidemiology (STROBE) initiatives for cohort studies ([32] STROBE checklist can be found in Additional file 1).

This study encompasses three sources of data collected at baseline and 12 months follow-up: 1) client surveys; 2) semi-structured interviews with clients and stakeholders; and 3) housing and support program data.

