**Discussion:**

This study will systematically evaluate the efficacy of a scatter site model (Platform 70) and a congregated model (Common Ground) of the Housing First approach; an examination that has not yet been made either in Australia or internationally. A clear strength of the study is its timing. It was designed and implemented as the programs in question themselves were introduced. Moreover, the programs were introduced when the Australian Government, with State and Territory support, began a more focused, coordinated response to homelessness and funded rapid expansion of innovative homelessness programs across the country, including Common Ground supportive housing developments.

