### Aims

While the Housing First approach has been evaluated internationally [27,20,28,29] and is being keenly applied in Australia, there has been a paucity of evidence on the effectiveness of Australian adaptations of the approach. Findings from evaluations of individual Housing First programs within Australia have recently been released publicly [30,31], however no study examining more than one of these adaptations with the same methodology has been conducted. Further, evaluations to date have focused largely on housing sustainability rather that incorporating broader measures of health and quality of life. Given this, there remains a pressing need to determine the efficacy of these respective models (Platform 70 [scatter site]; Common Ground [congregated site]) in relation to both housing and health outcomes. In response to this gap in the evidence-base, we have commenced a longitudinal analysis of these two adaptations using a standardised mixed methods approach to examine the changes in housing and health outcomes associated with the respective models.

Specifically, we aim to:Determine whether changes occurred with respect to clients’ housing stability, physical and mental health and treatment rates, psychological distress, quality of life, substance use patterns, and health and criminal justice system contact.Identify the demographic and social characteristics of clients that predicted success in each model. For the purposes of this study, success was defined as sustained tenancy and improved health and well-being outcomes.Calculate the net of ‘cost offsets’ of the two programs; that is, the reduction in measurable health, criminal justice and other costs borne by government as a consequence of the program.

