### Data analysis

Given the nature of the housing programs under evaluation, we were limited by the number of clients engaged with each program and therefore did not perform a formal power-based sample size calculation. Instead, we invited all eligible Platform 70 and Common Ground clients to participate in the client survey, and recruitment continued until all eligible clients had either provided consent or declined participation in the research.

Loss to follow-up comparisons that assesses the characteristics of participants in the two programs who completed both baseline and follow-up client surveys (completers) against those who only completed the baseline survey (non-completers) will be made. The purpose of these comparisons is to determine whether there are any key differences between survey completers and non-completers of each program. Other patterns of missing data will be examined to determine if there are potential biases. Appropriate literature that addresses how to deal with missing data and small populations and/or small samples will also be consulted.

To address Aims 1 and 2, a profile of clients engaged with the two housing programs will be constructed, which will include demographics, homelessness history and health status. Multivariate analysis will be undertaken to determine changes over time (baseline to follow-up) in key outcomes, including housing, health status and treatment rates, quality of life, substance use patterns, and contact with the health and criminal justice systems within and across the two programs. Additionally, multivariable logistic regression will be used to identify factors associated with sustained tenancies using SAS version 9.4 software.

Qualitative interviews with clients and stakeholders will be thematically analysed in line with the general inductive approach using NVivo 10 software. The analysis will identify key themes in sustained and failed tenancies. These data will be presented in such a way as to give some indication of the commonality or otherwise of particular views, but will not purport to be representative.

To address Aim 3, the cost to government of mainstream health and criminal justice service use by Platform 70 and Common Ground clients and how this use changed over time will be examined. It will also review the cost of delivering the programs and the extent to which this is offset by a decrease in the cost of mainstream government services use by participants.

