### Strengths and limitations

A key strength of this study is that it is uniquely positioned to provide robust evaluative evidence of the efficacy of these housing programs within an Australian context. The timing of this study is particularly critical due to the recent rapid development of Common Ground buildings throughout Australia, despite the lack of published empirical research to support the expansion of the model [26]. A further strength of the methodology is the extensive recruitment and follow-up procedures in place. The success of these procedures to recruit and follow-up with transient clients will provide a template for future research with vulnerable and homeless populations.

It is important to acknowledge the limitations of this evaluation. First, individuals housed through these programs had chronic homeless histories and were identified as requiring priority housing due to their high level of vulnerability. Subsequently, the findings have limited generalizability to the full homeless population in Sydney. Second, the methodology is mostly reliant on self-report measures, which may affect reporting accuracy due to factors such as memory error, nondisclosure, social desirability or intentional misrepresentation [48]. To reduce the chance of this occurring, a recall timeframe of 12 months or less and visual show cards were used, as were standardised tools validated for use with vulnerable populations [49]. It was noted during the study design that previous studies have demonstrated a moderate to high internal consistency in self-reports by individuals experiencing homelessness, including those with severe mental health conditions [50,51]. Additionally, all participants were informed that their client surveys and qualitative interviews were confidential and their responses would not affect their relationships with housing or support services. The final limitation is the small sample sizes. However, the nature of the programs means that the population from which to recruit from was also small. Despite this, substantial time and resources were devoted to contacting every eligible client to ensure that everyone had an opportunity to participate, including going on street patrols and spending days shadowing case managers. Significant efforts have also been made to identify appropriate analytical techniques for small samples.

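### Placement by need, no control group and one program per model do not support the article's efficacy and cost-consequence claims, and the limitations do not say so

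*Protocol article*

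**What the plan says.** - **Allocation.** Under Study design the article states: "The process of allocation to the two housing programs was determined by needs analyses conducted by the case workers who engaged with homeless individuals". Because of this process, "a control group was not a feasible option and an ecological study was selected which utilised a longitudinal, mixed methods design".
- **One program per model.** The Background describes Platform 70 as the scatter-site program and Common Ground Sydney as the congregated one. No other program represents either model.
- **Comparison.** The same section reports: "Housing and health outcomes were compared at baseline and 12 months follow-up of the scatter site (Platform 70) and congregated site (Common Ground) programs". Data analysis plans multivariate analysis of change in outcomes, ending with "contact with the health and criminal justice systems within and across the two programs".
- **Claim.** The Discussion part of the Abstract says: "This study will systematically evaluate the efficacy of a scatter site model (Platform 70) and a congregated model (Common Ground) of the Housing First approach". Aims: "there remains a pressing need to determine the efficacy of these respective models". Strengths and limitations says of the study that "it is uniquely positioned to provide robust evaluative evidence of the efficacy of these housing programs within an Australian context". Aim 3 defines cost offsets as government costs that fall because of the program.
- **Limitations.** Three are listed: generalisability, self-report and small samples. Client vulnerability appears only as a reason for limited generalisability, not as something that may differ between the programs.

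**The concern.** Efficacy is a causal word. To credit a between-program difference to the model, the two client groups would have to be comparable apart from the model, and the program-specific features would have to be separable from it. The article says that placement followed an assessment of need, and need plausibly bears on tenancy, health, service use and justice contact. With one program per model, the provider, the source of housing and the support arrangements all travel with the model. The cost claim has a related weakness: a before-and-after comparison without controls cannot show that the program caused the fall.

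What is at stake is use of the results. The article ties the study's importance to the rapid expansion of Common Ground buildings and to housing policy. A contrast that is open to confounding, but billed as robust evidence of efficacy, could be used for or against a model.

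**Working it through.** The article states no power, alpha or effect size, so there is no planned figure to reproduce. Its descriptive rates do reproduce: recruitment 80/122 = 66%, 45/70 = 64% and 35/52 = 67%; retention 63/80 = 79%, 37/45 = 82% and 26/35 = 74%.

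**Step 1: are the groups known to be comparable?** Need is not tabulated. In Table 1 the full client populations are close on sex (83% v 77% male) and mean age (43 v 44 years). They differ on Indigenous status (28% v 14%) and on birth in Australia (86% v 74%). This shows that the populations are not identical; it does not show that need differs.

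**Step 2: is the basis of allocation among the data?** The survey measures and the program data are itemised. The needs-analysis result is in neither list.

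**Step 3: can baseline values stand in for need at placement?** Only partly. The programs opened in August and November 2011. Baseline surveys ran from November 2012 to May 2013, which is 15 to 21 months after the first opening and 12 to 18 months after the second. Eligible clients could already be housed. Health, cognition and service use at baseline may therefore already reflect the program. Age, sex, Indigenous status, schooling and homelessness history before entry do not have this problem.

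**Step 4: precision of a cross-program contrast.** With 37 and 26 completers:

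SE = √(1/37 + 1/26) = 0.256 SD; 95% half-width = 1.96 × 0.256 = 0.50 SD; difference detectable with 80% power = (1.96 + 0.84) × 0.256 ≈ 0.72 SD.

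This is for a follow-up comparison without baseline adjustment. If baseline were adjusted for, with an assumed baseline-to-follow-up correlation of 0.5 to 0.7, the half-width would be 0.50 × √(1 − ρ²), or 0.43 to 0.36 SD.

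**Step 5: illustration of bias (all inputs assumed, no true model effect).** Let d be the need difference between programs in SD and r the correlation of need with outcome. Then bias = d × r, and the chance of a nominally significant result is Φ(bias/SE − 1.96) + Φ(−bias/SE − 1.96).

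| d | r | Bias (SD) | Chance of p < 0.05 |
|---|---|---|---|
| 0.2 | 0.3 | 0.06 | 6% |
| 0.3 | 0.5 | 0.15 | 9% |
| 0.5 | 0.5 | 0.25 | 16% |
| 0.8 | 0.7 | 0.56 | 59% |

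More participants would shrink the SE but not the bias. No sample size separates model from program when there is one of each.

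**The case against.** The strongest reply is that the article never announces a test of one model against the other. Aim 1 asks whether changes occurred, Aim 2 looks for predictors of success in each model, and the Aims section once describes the purpose as examining changes associated with the models. The absence of a control group is openly explained in Study design and defended again in the Discussion. The analysis is called multivariate, baseline characteristics are collected, and a condensed article need not list its adjustment terms. Both programs also drew on the same catchment and outreach service and required a history of chronic homelessness.

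Much of this stands:
- A reader might infer that the study is built to declare one model superior. The text does not say that.
- A reader might infer that placement followed severity. The article says only that needs were analysed, which could mean matching the type of support.
- A reader might infer one site per model. That is wrong for Platform 70, whose 70 units are scattered across Sydney; the accurate statement is one program per model. Dispersed against single-building housing is also part of what defines the models.
- An unlisted covariate set is not a finding here.

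What does not fall away is the wording. Efficacy appears in the Abstract, the Aims and the Strengths, and causal language in Aim 3. The article's own association wording conflicts with these. An analysis plan would not correct the claims or the limitations list in this document.

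**Conclusion.** The point holds as a mismatch between design and claim. Need-based placement, no control group and one program per model mean that cross-program differences may reflect client need or the particular program. The article describes its results in causal terms and omits these features from its limitations.

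The size of any bias is unknown. The range of 0.06 to 0.56 SD rests entirely on assumed need differences of 0.2 to 0.8 SD and correlations of 0.3 to 0.7. It refers to a follow-up comparison, and stable differences would partly cancel in change scores. It shows only that a bias could be comparable to the study's resolution of roughly 0.36 to 0.50 SD. A reader might go further and conclude that the contrast is biased by a definite amount, or that it is certain to be misread as a model effect. The document supports neither.

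**What to change.** 1. Make change within each program the main result, and label cross-program contrasts as non-causal. Within-program change is itself uncontrolled, so item 3 applies to it as well.
2. Show cross-program contrasts both unadjusted and adjusted for a small set of factors fixed before placement and already collected: age, sex, Indigenous status, schooling, and homelessness history before program entry. Add the needs-analysis result only if it was recorded and can be retrieved; the article does not show that it was. Leave out cognition, diagnoses and days housed as adjusters, because they may post-date placement.
3. Replace *efficacy* (Abstract, Aims, Strengths) and *as a consequence of* (Aim 3) with the *associated with* wording already in the Aims.
4. Add to the limitations: allocation by need, no control group, and one program per model.

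Items 1, 3 and 4 need only changes of presentation and wording. Item 2 uses existing data, at the price of slightly less precise cross-program estimates, and with 26 completers in the smaller group the covariate set must stay short. The overall claim becomes more modest. Adjustment will not separate model from program; only the wording can deal with that.

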### Participants, setting and measures

#### Client surveys

Eligibility criteria to participate in the client surveys were that participants had to be at least 18 years old at baseline, were able to provide informed consent, had a history of chronic homelessness (more than six months history of sleeping rough), and were currently housed or waiting for housing with the Platform 70 or Common Ground programs. All individuals housed through these two programs had to firstly be engaged through the Way2Home assertive outreach program, and as such would have received support prior to entering either housing program.

Initially, all eligible clients were asked by their case manager whether they would consent to being approached by a trained researcher to explain the details of the study. All clients who agreed to participate were provided with a Participant Information Statement and Consent Form which they were asked to read and sign. If a participant was unable to read, all information and instructions were read aloud. The survey was then administered by a trained researcher who read the questions to the participant and recorded their responses in a pen and paper format. Upon completion, the survey was sealed in an envelope and returned to the research supervisor for a quality control check (see Additional file 2 for further information on recruitment process).

Surveys were conducted in a neutral public space that was convenient and comfortable for the participant, such as a park, café or an available consultation room at Common Ground. As compensation for their time and travel, participants were offered an AUD$40 food voucher [33]. All researchers completed a three-hour training session on administering the client survey and adhering to an interviewer safety protocol [34]. On average, surveys took 45 minutes to complete.

To reduce loss at follow-up, a systematic process for locating and communicating with participants for the follow-up survey was implemented (see Additional file 3). With their consent, at baseline participants filled out a Locator Form asking them for their primary contact information (e.g., phone number, mailing address, email address) and the contact information for family, friends or service providers with whom they have regular contact. The form provided space for participants to note down any specific instructions for contacting them or their nominated contacts. Participants were also asked to sign a Release of Information Form, which provided consent for the researchers to obtain their contact details from Centrelink (a government agency responsible for welfare payments) if other methods of follow-up were not successful. This form provided space for participants to record their Centrelink client identification number to facilitate record access and matching. Signing the Locator and Release of Information forms were voluntary and a decision not to sign either form did not exclude participants from being involved in the research.

In total, 80 participants were recruited at baseline, which equated to a recruitment rate of 66% (Platform 70: 45 of 70 clients recruited, 64%; Common Ground: 35 of 52 clients recruited, 67%). Reasons for non-recruitment included refusal, unable to make contact, non-English speaking, incarcerated and away during the recruitment timeframe. Baseline data collection occurred from November 2012 to May 2013. As shown in Table 1, the demographic compositions of the two samples are mostly similar to that of all clients within the programs.

**Table 1 Tab1:** **Demographic composition of the client survey samples recruited at baseline compared to the overall populations**

**Demographics**	**Platform 70 (scatter site)**		**Common Ground (congregated site)**	
	**Sample (n = 45)**	**Population (N = 70)**	**Sample (n = 35)**	**Population (N = 52)**
Sex (% male)	84	83	77	77
Mean age (years)	44	43	44	44
% Indigenous	20	28	10	14
% born in Australia	82	86	73	74

For the 12-month follow-up survey, the participant retention rate was 79% (Platform 70: 37 of 45 participants, 82%; Common Ground: 26 of 35 participants, 74%), which is comparable with longitudinal studies of Housing First programs internationally [29,35]. Follow-up surveys were conducted from October 2013 to May 2014. Nine baseline Platform 70 participants did not complete the follow-up survey due to not being contactable (n = 6), refused (n = 2) or incarcerated (n = 1). Similarly, nine baseline Common Ground participants did not complete the follow-up survey due to not being contactable (n = 6), refused (n = 1), incoherent (n = 1) or passed away (n = 1).

The following measures were collected at both baseline and 12-month follow-up surveys, with the exception of some demographic variables that would not change over time (e.g., sex). To maximise the sample sizes, all eligible Platform 70 and Common Ground clients were invited to participate in the client survey, and recruitment continued until all eligible clients had either provided consent or a reason for non-participation in the research had been ascertained.

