### Housing first program 1: scatter site

Platform 70 is a Sydney-based Housing First program that commenced in August 2011. The program is government funded to head-lease 70 units of housing stock from the private rental market scattered across Sydney. Clients housed through Platform 70 were provided wrap-around support services to ensure their tenancies were successfully maintained. Accessing housing from the private rental sector (through a community housing head-lease arrangement) is an innovative approach that increases the housing options available to people sleeping rough. The public housing stock has decreased significantly in Australia and demand for public housing from very low income earners, homeless individuals and their supporting agencies far outstrips supply [25]. The private rental housing market represents a critical, but hitherto under-utilised option for transitioning from homelessness, and the immediacy and diversity of the private rental market can assist with achieving rapid access to housing.

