### Housing first program 2: congregated site

The second Housing First program which will be examined in this study is Common Ground Sydney, which opened in November 2011. Common Ground provides social housing accommodation with a community housing provider managing tenancies. This socially integrated housing complex comprises 104 apartments, half of which were allocated to individuals with a chronic homelessness history [23] and the other half to priority social housing and affordable housing tenants. On-site extensive health and social support services are available to all tenants, as well as a link to a social enterprise. The Common Ground model has been rapidly expanded across Australia, with nine other Common Ground buildings either under construction or in operation between 2008 and 2013 [26].

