A detailed examination of mainstream services will utilise the health and criminal justice system contact data collected in the client surveys. Associated costs incurred in the 12 months prior to the baseline client survey will be compared with the cost of services used in the 12 months prior to the follow-up client survey. The cost of health and justice services will also be compared with the NSW population average.

The cost of health and justice services used by client survey participants will be estimated by applying the unit cost for each service to reported use. Unit costs will be estimated from publicly available information including the Report on Government Services 2013 [42] and various other reports, including those published by the Australian Institute of Health and Welfare [43-47]. These sources will also be used to estimate average service use and associated cost for the NSW population.

The cost of delivering the Platform 70 and Common Ground programs will be examined with reference to recurrent expenditure for the period in which clients were housed in the program. We shall also consider the range of rental subsidies provided to clients in the two housing models. Funding and expenditure data will be sought directly from the providers of social, health and tenancy management, and administrative services. To estimate the recurrent cost incurred by housing providers to manage and maintain properties, we shall draw on estimates obtained from the Report on Government Services [42]. Platform 70 and Common Ground case workers potentially provide more time to resolving issues associated with their tenancies than is normal. This implies that the average recurrent cost/dwelling is likely to represent a conservative estimate of the cost incurred by housing providers.

Housing providers also incur the capital cost of accommodation. In our cost analysis we will only consider public and community housing capital costs in the Common Ground program as Platform 70 involves the head leasing of privately owned dwellings. The average capital value of public housing and community housing properties available to Common Ground clients will be established and the annualised value of capital employed estimated by applying an opportunity cost of capital of 8% [42] to the average capital value.

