## Discussion

### Contributions

Given the chronicity of homelessness in Australia, a novel housing policy approach to reducing homelessness has been recently introduced. The housing programs are based on the Housing First approach, whereby individuals who are chronically homeless are offered a tenancy, without first having to be housing-ready. This study will address an important gap in both the public health and housing literature by examining the nature and extent of changes for clients upon being placed in one of the two variations of the Housing First approach; Platform 70 (scatter site model) or Common Ground (congregated model). Additionally, this study will document the journeys of a sample of people in the programs by recording their individual changes over time as they are placed into one of the long-term housing programs available.

Housing and health are inextricably linked and evaluations of housing policy should measure outcomes across both domains. Whilst randomised controlled trials are the gold standard approach for much health research, they are not the most appropriate methodology when assessing the impact of programs that deliver housing and the denial of the intervention (housing) to a control group is not an option. In this situation, a longitudinal mixed-methods approach using standardised and validated measures is appropriate.

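### Baseline was surveyed 12 to 21 months after the programs opened, with already-housed clients eligible, so the before-after change and the Aim 3 offset do not measure change on being housed

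*Protocol article*

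**What the plan says.** Under Client surveys, eligible people "were currently housed or waiting for housing with the Platform 70 or Common Ground programs". The same section states that "Baseline data collection occurred from November 2012 to May 2013" and that "Follow-up surveys were conducted from October 2013 to May 2014".

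The two program descriptions give the start dates: "Platform 70 is a Sydney-based Housing First program that commenced in August 2011", and "Common Ground Sydney, which opened in November 2011".

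For Aim 3, Data analysis fixes the comparison: "Associated costs incurred in the 12 months prior to the baseline client survey will be compared with the cost of services used". The second window is the year leading up to the follow-up survey. The Aims section defines the cost offset as a reduction in government costs brought about by the program. For Aim 1, Data analysis plans change from baseline to follow-up, within and across programs. It does not anchor that change to the date of housing or separate housed from waiting clients.

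Contributions says the study will examine "changes for clients upon being placed in one of the two variations of the Housing First approach". The Discussion paragraph of the Abstract says of the study: "It was designed and implemented as the programs in question themselves were introduced". Strengths and limitations does not mention housing status at baseline.

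**The concern.** A before-after design measures the effect of an event only if the first measurement precedes it. Here the event is entry to housing, and the first measurement could follow it by more than a year. To the extent that health, service use or justice contact changed on entry, that part lies before or inside the baseline window. It is then missing, or partly missing, from the difference.

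Aim 3 is the most exposed. Program cost is counted for the period in which clients were housed, while the saving is a difference between two years that may both contain housed time. If mainstream service use fell on entry, the offset is understated relative to the cost. For Aim 1, a small change could be read as no benefit from placement when it describes a year within a tenancy. The programs opened three months apart, so time already housed may also differ between them, which bears on the comparison across programs.

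**Working it through.** **Inputs.** Platform 70 start: August 2011. Common Ground opening: November 2011. Baseline: November 2012 to May 2013. Look-back for service use and cost: 12 months. All are from the Protocol article. It gives no entry dates and no count of clients housed at baseline, and no figure of its own to reproduce.

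**Step 1: lag from opening to baseline.**
- Platform 70: August 2011 to November 2012 = 15 months; to May 2013 = 21 months.
- Common Ground: November 2011 to November 2012 = 12 months; to May 2013 = 18 months.

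The earliest look-back starts 15 - 12 = 3 months after Platform 70 began and 12 - 12 = 0 months after Common Ground opened. No part of any look-back year clearly precedes either program.

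**Step 2: places and clients.** Platform 70 has 70 units and 70 clients. Common Ground has 104/2 = 52 apartments for people with chronic homelessness, and 52 clients. This suggests programs at or near capacity but does not prove it, because waiting clients were eligible too.

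**Step 3: housed share of the look-back year, by assumption.** Let L be the months from opening to survey and T the months housed at survey. The housed share is the mean of min(12, T)/12.
- Even intake, T uniform on 0 to L (L at least 12): 1 - 6/L.
- Later-half intake, T uniform on 0 to L/2: L/48.
- Early-half intake, T uniform on L/2 to L: 2(1 - 6/L) - L/48.

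| Intake (assumed) | Platform 70, L = 15 to 21 | Common Ground, L = 12 to 18 |
|---|---|---|
| Later half | 15/48 = 31% to 21/48 = 44% | 12/48 = 25% to 18/48 = 38% |
| Even | 1 - 6/15 = 60% to 1 - 6/21 = 71% | 1 - 6/12 = 50% to 1 - 6/18 = 67% |
| Early half | 89% to 99% | 75% to 96% |

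Under even intake, the share of clients housed for the whole look-back year is 1 - 12/L: 20-43% for Platform 70 and 0-33% for Common Ground. All three patterns treat every client as housed by the survey. If a fraction w is still waiting, the shares in the table are multiplied by 1 - w.

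**Step 4: what the difference can show.** Suppose service use steps down on entry and the follow-up year is fully housed. The visible part of the step is then 1 minus the housed share. Even intake leaves 29-40% visible (Platform 70) and 33-50% (Common Ground). Across all patterns in the table the range is 1-75%.

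**Step 5: short-recall measures.** The BSI covers seven days, the WHOQOL-BREF two weeks, and recent substance use three months. Anyone housed for longer than the recall period has no unhoused baseline on that measure.

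**The case against.** A reader might infer that the study mainly compares one housed year with another and that nearly all of the effect is hidden. The documents do not support that. They give no entry dates, and waiting clients were expressly eligible. Client numbers equal to places do not establish full occupancy: the 70 units are a funded number, and the client count may include people waiting. Under late intake, more than half of a step change would remain visible.

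A reader might also infer that Aim 1 is necessarily biased toward no change. That holds only if improvement is prompt on entry; gradual improvement during a tenancy would still appear. Aim 1 itself asks only whether changes occurred, and the Aims section speaks of changes associated with the models. The Abstract's remark on timing covers design as well as implementation, and the start of design is undated, so only the word for implementation conflicts with the dates.

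These points limit the size and the wording. They do not remove the mismatch. The article itself fixes the cost windows, attributes the offset to the program, and promises change on placement, so this is not a detail left to an analysis plan.

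**Conclusion.** The point stands in a limited form. It is certain that baseline fell 15-21 months (Platform 70) and 12-18 months (Common Ground) after opening, that already-housed clients were eligible, and that the Aim 3 windows are therefore not before and after housing for those clients. It is probable, but unreported, that their share is substantial.

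How much of the look-back year was housed depends on assumed intake: about 25-44% if late, 50-71% if even and 75-99% if early, and less if some clients were still waiting. The understatement of the offset and of change on placement is conditional on use or health having changed on entry. As planned, the comparison delivers neither a cost reduction caused by the program nor change upon placement.

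**What to change.** - From the participant-level 12-month housing calendars collected at both surveys, compute each participant's housed days in the two look-back windows, and report them by program.
- Report Aim 1 and Aim 3 changes separately for participants waiting and already housed at baseline. Describe results for the latter as change during tenancy. Even the waiting group had Way2Home outreach support, so it is unhoused but not unsupported.
- Regress change in 12-month service use and cost on change in housed days. Use cannot be assigned to individual housed or unhoused days, because the survey records 12-month totals.
- In Aim 3, set the change in mainstream costs against the difference in program cost between the same two windows.
- Use program tenancy data only if they can be linked to participants; the days-housed data are described as de-identified.
- Reword Aim 3, the Contributions paragraph and the Abstract's claim about implementation, and add the point to the limitations.

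The cost is wording and modest extra analysis on data already collected. Baseline itself cannot be changed. With 37 + 26 = 63 participants followed up, the waiting subgroup may be small and its intervals wide.
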